## 4.4 HIV Care Services

The south-western high density suburbs are serviced by two infectious disease hospitals (Wilkins Hospital and Beatrice Road Infectious Disease Hospital) at which all children under 16 years who test HIV positive are assessed and initiated on ART if eligible. Patients who are diagnosed following admission to the two central hospitals (Parirenyatwa or Harare Central Hospitals) may elect to receive their care at the HIV clinics at these two hospitals.

ART is initiated at Hospital HIV outpatient services but HIV treatment is decentralised to primary care once patients are stable on treatment. Thus, patients aged over 10 years are monitored for a period of three months after initiation of ART, and then they are transferred to their nearest Primary Health Care Clinic for continuation of treatment. Children aged below 10 years usually continue to receive ART at secondary care services.

For those not ready for ART initiation, there is no formal pre-ART care at present, although all HIV-infected patients are provided with life-long cotrimoxazole obtained from PHCs and are supposed to have twice yearly CD4 counts.

The treatment programme is well-functioning and there have been no major stock-outs of paediatric or adult formulations of ART drugs in Zimbabwe during 2011. Apart from the National AIDS Trust Fund, the country has been getting support from different partners for the ART programme. Most of the paediatric formulations are funded by Clinton Health Access Initiative (CHAI) Zimbabwe. The figure 4.1 shows the relative contributions by the major ART funding partners in 2011.

**Figure 4.1 Total ART patient support by funding partners 2011**

[figure not shown]

***Source: MOHCW 2011 ART Update***

A total of 463,361 clients were on ART in Zimbabwe by end 2011, out of the 593,000 in need of ART, with a 35% increase in coverage from 2010 to 2011. In terms of national coverage, Zimbabwe is now at 78.1% of those who urgently require ART. The patient survival rate for 2011 was 78% and 69% for 12 months and 24 months respectively.

In 2010 Harare City Health Clinics registered approximately 2,000 new HIV patients aged between 5-14years and 45% of them were from the South-Western High Density Suburbs. (HARARE CITY HEALTH Annual Report 2010)

**Table 4.3 Data on ART coverage 2011 (National ART programme)**

|  | **ZIMBABWE** | | **HARARE only** | | **STUDY SUBURBS only** | |
| --- | --- | --- | --- | --- | --- | --- |
|  | Children (<15years) | Adults | Children (<15years) | Adults | Children (<15years) | Adults |
| **Eligible for ART** | 2,006 | 19,934 | 96 | 1,750 | 11 | 167 |
| **Ever Initiated** | 44,877 | 477,706 | 8,963 | 97,525 | 1,821 | 9,859 |
| **Transferred Out** | 80 | 1,644 | 7 | 945 | 5 | 27 |
| **Transferred In** | 168 | 1,366 | 9 | 530 | 1 | 44 |
| **Currently On 1st Line ART** | 40,273 | 415,991 | 8,793 | 75,028 | 1,821 | 3,155 |
| **Currently On 2nd Line ART** | 332 | 6,765 | 150 | 4,199 | 62 | 99 |
| **Lost** | 247 | 870 | 61 | 136 | 0 | 14 |
| **Deceased** | 52 | 564 | 5 | 39 | 0 | 4 |

First and second-line treatment options and fixed-dose combinations (FDCs) with scored tablets are available for children. National ART Guidelines criteria (from May 2010) for starting ART in children are summarised below:

1. Paediatric WHO Clinical Stage 3 or 4 disease, irrespective of CD4 count or CD4%
2. Immunological criteria:

| **Immunological marker** | **Age-specific criteria for initiating ART** | | |
| --- | --- | --- | --- |
| **Infant ≤24 months** | **>24-60 months** | **≥5 years** |
| CD4 % | Treat all irrespective of CD4 count/ CD4% | <25% | N/A |
| CD4 count | <750cells/µl | <350cells/µl (as for adults) |

## 4.5 Participant selection, inclusion and exclusion criteria

The inclusion criteria for participation in the trial will be:

- age between 6 years (day of their 6th birthday and older) and 15 years (a day before their 16th birthday)
- test HIV-positive following PITC in the PHC
- willing to have their HIV care at the PHC
- usual residence in the study suburb where the PHC is located
- informed consent by parent and assent from child to participate

The exclusion criteria for participation in the trial will be:

- age <6 years or ≥16 years
- usual residence outside the study suburb where the PHC is located
- previously tested HIV+ positive and receiving care (clinical or psychosocial)
- not planning to access HIV care at the PHC

All participants enrolled into the trial will automatically be offered enrolment into the cohort study. Additionally, any children aged 6-15 years who test HIV-positive following PITC after enrolment for the trial is completed, will also be approached for recruitment into the clinical cohort study.

# METHODS AND PROCEDURES

## 5.1 Routine PHC based PITC

All children aged 6-15 years attending for acute care at primary health care clinics (PHC) in seven of the 10 high density suburbs of southwest Harare (Highfield, Glen View, Budiriro, Kuwadzana, Mufakose, Dzivarasekwa, Glen Norah) will be offered routine provider-initiated testing and counselling (PITC) during a two year period. Training on HIV testing and counselling of children will be provided through PSI.

A research assistant will be based at the clinic and will identify children eligible for PITC and refer them for HIV testing to PHC counsellors/nurses. After clinic registration, the standard approach to PITC developed by the Ministry of Health and Child Welfare will be used. All eligible clinic attendees will be given brief standard pre-test counselling followed by an offer of HIV testing and post-test counselling. Guardian consent will be required for children to undergo HIV testing. Children attending without a guardian will be given information about HIV testing and encouraged to re-attend with a guardian for HIV testing.

HIV test results will be given to the child and their guardian at the same clinic visit, with age-appropriate explanation of HIV test results given to the child. Children who test positive will be offered enrolment into HIV care at the PHC where they test. Biological parents, guardians and natural siblings of children who test HIV-positive will be offered HIV testing. Attendees who decline HIV testing will be assessed for their presenting health problem by the clinic nurse. PITC outcome will be recorded as accepted/ absent guardian/ testing for subject declined /testing for guardian declined.

HIV testing kits will be provided by the National HIV Program. The research assistants will ensure that a supply of testing kits is always available at the PHCs. Diagnostic HIV testing will be carried out using two HIV rapid tests (Abbott Determine™ and SD Bioline™) run in parallel. Discordant specimens will be resolved using a third rapid HIV test (INSTI™).

## 5.2 Implementation of Decentralised HIV care in PHCs

Nurse-led HIV care services for children will be established in the six PHCs that offer PITC. A designated nurse from each of the six PHCs will be invited to training course on paediatric HIV care at first-level facilities. The course will integrate HIV care with the IMCI clinical guidelines, as well as additional training on adolescent HIV care issues.

HIV care services at the PHC will include cotrimoxazole prophylaxis, routine follow-up visits, management of intercurrent illness as done within the routine primary health system (+emergency visits and referral to secondary care if indicated), disclosure and adherence counselling.

ART regimens and starting criteria will be dictated by National policy and practice, with drugs provided by the National ART Programme. Current National ART guidelines are summarised below:

| **Nevirapine-Exposed** | **Non-exposed** |
| --- | --- |
| ***First-line Treatment*** | |
| Stavudine+ lamivudine+ PI* | Stavudine+ lamivudine+ nevirapine |
| ***Alternative First-line Treatment*** | |
| Zidovudine +lamivudine + PI* | Zidovudine + lamivudine + nevirapine |

*Note: HIV-infected infants exposed to nevirapine (NVP) through infant or maternal treatment or prophylaxis, especially single-dose nevirapine, may have viral resistance*

**Current PI used is lopinavir/ritonavir*

*Abacavir and didanosine available as second-line drugs, in combination with PI or NVP (changing to the drug class that hasn’t been used in the first line regimen)*

At each follow-up visit, a standard symptom screen will be carried out and incident clinical events, adherence, height and weight recorded. At each visit, a prescription of ART will be given, with dose adjustment as required. Those starting ART will be seen every two weekly for the first month, monthly for the next two months, and three-monthly thereafter. Those not taking ART will be followed up at two weekly for the first month and three monthly thereafter.

Routine HIV care will be provided by PHC nurses. The research team will consist of a qualified nurse and a research assistant, with each team responsible for two PHCs. The research team will be responsible for identifying attendees eligible for PITC, supporting HIV care provision and collection of clinical cohort data. The study physician will be responsible for all 6 PHCs and will consult at the PHCs every two weeks and supervise the PHC HIV care providers, provide training updates and see complex cases. Ongoing mentoring for primary care nurses will be provided by City health doctors who consult at PHCs on a weekly basis.

## 5.3 Randomisation and investigator blinding

Eligible participants who reside in the study suburb where the PHC is located will be randomly allocated to either standard HIV care or to standard care + the support intervention (1:1 in each clinic). If the child resides outside Harare, he/she will be offered standard clinic care but will be excluded from the trial and the cohort study. All children aged 6-15 years registering for HIV care at the clinic and resident in Harare will be invited to participate in the cohort study, even if they refuse participation in the trial. The PI will be blinded to the information on the trial arm each participant is allocated to until the end of the trial follow-up.

**5.3.1 Randomisation Procedure**

Randomisation will use proportional stratified random sampling using computer generated pseudo –random numbers. The size of each strata will be proportionate to the population size of children aged 6-15 years who are serviced by the clinic (based on Census 2002 data) and are expected to be HIV positive (based on extrapolations from previous surveys in the same study suburbs)

- Stratification will be according to the recruitment clinic (6 clinics)
- The sampling fraction will be 0.175 to ensure that each clinic is allocated study numbers proportional to the expected population of children aged between 6-15 years who test HIV positive (sample which is proportional to size)
- Random allocation to either standard HIV care or to standard care + the support intervention of 1:1 at each clinic will be done, thereby each study number allocated to the clinic will be randomly allocated to either standard HIV care or to standard care + the support intervention
- As the children are recruited into the study, a study number will be allocated consecutively and the appropriate study arm linked to the number.

In the event that the child refuses to participate in the trial and/or is recruited in the cohort only a different study number will be allocated.

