## 1.3 Methodology

All children aged 6-15 years attending for acute care at primary health care clinics (PHC) in seven high-density suburbs of southwest Harare will be offered routine HIV counselling and testing during a two year period. The effectiveness of PHC-based routine PITC in providing high coverage of HIV diagnosis will be assessed through a prevalence survey for undiagnosed HIV infection in the 8-17 year age-group in the suburbs served by the PHCs. The seven PHCs will also provide decentralised HIV care, including antiretroviral therapy (ART) initiation.

Children who test HIV-positive through PITC at the PHCs will be recruited into an individual randomised trial of a voluntary lay worker (VLW)-delivered intervention to support households of HIV-infected children aged 6-15 years. Participants will be randomly allocated to either a) primary care based HIV care or b) primary care-based HIV care plus treatment support provided by VLWs, aim, aiming for equal number of control and intervention participants in each clinic. The intervention will be delivered over a eighteen month year period, the main outcomes being adherence to ART, and retention in care.

Children receiving HIV care at the PHCs including those recruited into the trial will be recruited into a clinical cohort study. Data from routine clinic visit (including height, weight, clinical symptoms, incident clinical events and adherence) will be collected. In addition, detailed growth monitoring, lung function testing and a psychosocial assessment (i.e. schooling, guardianship, and disclosure) will be carried out at pre-defined intervals. The rate of lung function decline and rates of pubertal development and growth will be compared by ART status, to investigate whether current ART initiation guidelines can prevent or delay progression of chronic lung disease and/or growth failure.

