## 4.2 HIV diagnosis and care services

Overall HIV prevalence in adults Zimbabwe has been declining and was estimated at 19.2% in 2011, 23.9% in 2010 and 30.6% in 2009 (National AIDS Council Annual Report, 2011). The adult HIV prevalence was estimated 19.1% in the study area during the 2008 DETECTB Household HIV Prevalence survey[[1]](#footnote-2). Estimates from the 2002 National Census indicated that there were approximately 120,182 children aged less than 16 years (mean 20,030, SD 4,409 children per suburb).

In a survey of 6 primary school located in the study suburbs, HIV prevalence among 6-14 year olds was estimated to be 2.7% (Table 4.1). Based on the DETECTB and School HIV Prevalence Survey estimates, the expected HIV prevalence among 6-14 year olds in the study suburbs was estimated to be approximately 14% of the adult prevalence, and thus estimated to range between 1.6% and 3.3%.

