**Table 4.1 HIV prevalence among adults and primary school children in Study Suburbs**

| **Suburb** | **Adult HIV Prevalence (%)**  *(DETECTB Survey 2008)* | **6-14 yrs HIV Prevalence (%)**  *Primary school Survey 2010)* | **Expected HIV Prevalence in 6-14 yr olds (%)** |
| --- | --- | --- | --- |
| Suburb 1 | 18.43 | - | 2.58 |
| Suburb 2 | 18.75 | 2.89 | 2.62 |
| Suburb 3 | 15.34 | 2.09 | 2.15 |
| Suburb 4 | 23.75 | 3.78 | 3.32 |
| Suburb 5 | 18.46 | 2.05 | 2.58 |
| Suburb 6 | 19.99 | - | 2.80 |
| Suburb 7 | 16.59 | 1.79 | 1.66 |
| **Average** | **18.75** | **2.52** | **2.53** |

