# HIV CLINICAL COHORT IN PHC

## 7.1 Eligible participants

Children aged 6-15 years who are test HIV positive at the seven study clinics and reside in Harare will be eligible for recruitment into the cohort study, regardless of whether they are eligible for recruitment into the randomised trial. Patients aged 6-15 years who are already on ART and accessing care at a secondary health facility will be offered HIV care at the study PHC they attend, but will not be eligible for recruitment into the cohort study.

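### The protocol counts six clinics in some sections and seven in others, and Table 5.1, from which study numbers are allocated, does not follow its own prevalence rule, sampling fraction or row order

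*Protocol*

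**What the plan says.** **Seven clinics.** Section 1.3 has testing at clinics in seven suburbs and adds "The seven PHCs will also provide decentralised HIV care, including antiretroviral therapy (ART) initiation". Section 5.1 offers testing "in seven of the 10 high density suburbs of southwest Harare" and names all seven. Section 7.1 takes into the cohort children who "test HIV positive at the seven study clinics and reside in Harare". Tables 4.1 and 5.1 each have seven rows.

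**Six clinics.** Figure 1.1, the study design in 3.3 and the choice of suburbs in 4.1 all use six. Section 5.2 says "Nurse-led HIV care services for children will be established in the six PHCs that offer PITC" and gives the study physician six clinics to cover. The stratification rule in 5.3.1 reads "Stratification will be according to the recruitment clinic (6 clinics".

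**Allocation.** Section 5.3.1 makes each clinic's study numbers proportional to its expected number of HIV-positive children, with a sampling fraction of 0.175. Table 5.1 carries this out: census population, prevalence, expected positives, fraction and final sample size. Section 4.2 gives the prevalence rule: among 6-14 year olds it is "estimated to be approximately 14% of the adult prevalence, and thus estimated to range between 1.6% and 3.3" per cent. The last suburb row of Table 4.1 (adult, school-survey and expected prevalence) is "Suburb 7 | 16.59 | 1.79 | 1.66".

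**The concern.** The number of strata and the count of study numbers per clinic are what the randomisation list is built from. A statistician who follows the sentence in 5.3.1 prepares six lists; one who follows Table 5.1 prepares seven. The table cannot settle the matter, because its columns do not follow from one another under the stated rule.

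Three things are at stake. First, which clinics are in the trial, and whether the nurse training and physician cover in 5.2 are meant for all of them. Second, the total: 350 is reached in Table 5.1 only with the seventh row. Third, the proportional representation of clinics that 5.3.1 sets out to secure. Study numbers are issued consecutively within a clinic, so a clinic given too few would use up its allotment early.

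**Working it through.** **Inputs.** Adult and expected child prevalence from Table 4.1; populations, expected positives and final sample sizes from Table 5.1; the 14% rule and census total from 4.2; the fraction 0.175 from 5.3.1; 175 per arm, 30% control rate, 45% reduction and 10% loss from 11.2.1.

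**1. Which clinics the background figures cover.**
- PHC1-6: 14,519 + 24,695 + 23,036 + 23,789 + 18,556 + 15,587 = 120,182. Their mean is 20,030 and SD 4,409. These are exactly the figures in 4.2. With PHC7 (19,203) the sum is 139,385.
- Adult prevalence, suburbs 1-6: 114.72/6 = 19.12%, against 19.1% in the text of 4.2. Table 4.1 averages seven suburbs and prints 18.75%.
- School survey, the four surveyed suburbs other than 7: 10.81/4 = 2.70%, against 2.7% in the text. Table 4.1 includes suburb 7 and prints 2.52%.

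So the text of 4.2 matches a six-suburb data set and the tables a seven-suburb one.

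**2. The 14% rule.** Expected prevalence = 0.14 × adult prevalence. Rows 1-6 give 2.58, 2.63, 2.15, 3.33, 2.58 and 2.80, against printed 2.58, 2.62, 2.15, 3.32, 2.58 and 2.80, so the rule reproduces them within rounding. Row 7 does not follow: 0.14 × 16.59 = 2.32, against 1.66, and 1.66/16.59 = 10.0%. The printed 318 does follow from 1.66% (19,203 × 1.66% = 318.8), so the departure lies in the prevalence and is carried into the count. At 2.32% the count is about 446. The lower bound of 1.6% in 4.2 rests on this row alone; under the rule the minimum is 2.15% and the seven-suburb average 2.62% instead of 2.53%.

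**3. The sampling fraction.** Expected positives total 3,540. 0.175 × 3,540 = 619.5, not 350. The fraction that gives 350 is 350/3,540 = 0.0989.

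**4. The row order.** Final sample size = expected positives × 0.0989:

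| Clinic | Expected positives (printed) | × 0.175 | × 0.0989 | Printed sample size |
|---|---|---|---|---|
| PHC1 | 375 | 65.6 | 37.1 | 32 |
| PHC2 | 648 | 113.4 | 64.1 | 37 |
| PHC3 | 494 | 86.4 | 48.8 | 64 |
| PHC4 | 790 | 138.2 | 78.1 | 49 |
| PHC5 | 479 | 83.8 | 47.4 | 78 |
| PHC6 | 436 | 76.3 | 43.1 | 47 |
| PHC7 | 318 | 55.6 | 31.4 | 43 |
| Total | 3,540 | 619.5 | 350 | 350 |

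From PHC2 down, each printed value is the proportional value of the row above. The 32 at PHC1 is PHC7's value: 31.4, taken as 32 so that the column sums to 350. Against the correctly placed column (37, 64, 49, 78, 47, 43, 32), PHC1, 2 and 4 are short by 5 + 27 + 29 = 61, and PHC3, 5, 6 and 7 are over by 15 + 31 + 4 + 11 = 61. That is 61/350 = 17% of the study numbers.

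**5. What the seventh row contributes.** The printed sizes sum to 350 over seven rows and 307 over six. With 30% against 16.5%, two-sided alpha of 0.05 (assumed) and 10% loss, 157 per arm gives 81% power, which reproduces the stated 80%. If the 43 places were dropped and not refilled, 138 per arm would give about 76%.

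**The case against.** A reader might infer that children at the seventh clinic have no stratum and no HIV care. The documents do not support this. Table 5.1 lists PHC7 under the stratum heading with 43 numbers, and the 350 includes them. Section 1.3 promises care with ART initiation at all seven clinics, and 5.1 offers care where the child tests. No section says that seven clinics test while six treat; that picture arises only from joining sections with different counts. Where a section covers both testing and care, it uses one count for both.

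A reader might also infer that PHC7 is short of study numbers because its prevalence is too low. Its printed 43 equals what the 14% rule would give, but only through the row displacement. On the face of the table there is no shortfall at PHC7.

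Three further points stand:
- The 14% is called approximate, and suburb 7's own school-survey figure of 1.79% is nearer to 1.66% than to 2.32%. There may be a reason for 1.66%, but none is given.
- Quotas do not bias the comparison of arms under 1:1 allocation within each clinic.
- Failure to reach 350 is not shown: PHC1-6 alone have 3,222 expected positives, and 11.2.1 sets no minimum per clinic.

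These points limit the harm. They do not remove the contradiction in the clinic count or the errors in the table.

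**Conclusion.** The concern holds as an internal contradiction together with a table that is wrong as written. The exact match of the census total in 4.2 to PHC1-6 suggests that a seventh clinic was added and the six-clinic text not updated, but this is an inference. Under the protocol's own proportional rule and printed prevalences, the fraction is too large by a factor of about 1.8 (0.175/0.0989) and 17% of study numbers stand at the wrong clinic. If the 14% rule is meant for every suburb, PHC7's expected positives are understated by about 128 (446 less 318).

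The effect is on the building of the randomisation list and on clinic representation, not on the validity of the comparison between arms. The fall in power to about 76% applies only if the PHC7 places were lost and never refilled. The correction should be made because it is specific and cheap.

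**What to change.** - **Settle the clinic count in every section:** Figure 1.1, 1.3, 3.3, 4.1, 4.2, 5.1, 5.2, 5.3.1, 7.1 and Tables 4.1 and 5.1.
  - If seven: state seven strata in 5.3.1, bring the care set-up and physician cover in 5.2 into line, and restate the background figures in 4.2 for seven suburbs.
  - If six: remove the seventh clinic and show how 350 is reached, since the printed PHC1-6 sizes sum to 307. Sharing 350 over 3,222 expected positives (fraction 0.1086) gives about 41, 70, 54, 86, 52 and 47.
- **Correct or justify suburb 7's 1.66%,** and with it the 1.6% lower bound in 4.2 and the 2.53% average.
- **Recompute all of Table 5.1,** including the fraction quoted in 5.3.1.
  - If 1.66% is kept with its reason: fraction 0.0989 and 37, 64, 49, 78, 47, 43, 32.
  - If 2.32% is used: 350/3,668 = 0.0954 and about 36, 62, 47, 75, 46, 42, 43. These rounded values sum to 351, so one must be rounded down.
- **Check the list in use.** If it has already been generated, compare it with the corrected table and record any difference.

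The cost is amendment wording and a re-derived table. The design and the target of 350 need not change.

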**Table 5.1: Expected sample size by suburb**

| **Stratum** | **Population Size**  **(2002 Census)** | **Estimated HIV Prevalence** | **Population Size (Expected HIV+ve)** | **Sampling Fraction** | **Final Sample Size** |
| --- | --- | --- | --- | --- | --- |
| PHC1 | 14519 | 2.58 | 375 | 0.175 | 32 |
| PHC2 | 24695 | 2.62 | 648 | 0.175 | 37 |
| PHC3 | 23036 | 2.15 | 494 | 0.175 | 64 |
| PHC4 | 23789 | 3.32 | 790 | 0.175 | 49 |
| PHC5 | 18556 | 2.58 | 479 | 0.175 | 78 |
| PHC6 | 15587 | 2.80 | 436 | 0.175 | 47 |
| PHC7 | 19203 | 1.66 | 318 | 0.175 | 43 |

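### Table 5.1 contradicts the proportional-allocation rule of section 5.3.1: the final-sample-size column is displaced down by one row, and the stated fraction of 0.175 would give about 620 children instead of 350

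*Protocol*

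**What the plan says.** Section 5.3.1 of the protocol sets the rule for clinic sizes: "The size of each strata will be proportionate to the population size of children aged 6-15 years who are serviced by the clinic", restricted to those expected to be HIV-positive. It then fixes one constant: "The sampling fraction will be 0.175 to ensure that each clinic is allocated study numbers proportional to the expected population". Each study number given to a clinic is randomised 1:1 to an arm, and numbers are issued consecutively as children are recruited.

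Table 5.1 carries the rule out. Every row shows the fraction 0.175. Two rows show the problem: "PHC4 | 23789 | 3.32 | 790 | 0.175 | 49" and "PHC1 | 14519 | 2.58 | 375 | 0.175 | 32". PHC4 has the largest expected count in the table.

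The same section describes the strata as follows: "Stratification will be according to the recruitment clinic (6 clinics". Table 5.1 has seven rows. The prevalence used for PHC7 comes from Table 4.1, whose row reads "Suburb 7 | 16.59 | 1.79 | 1.66". Section 4.2 says that expected child prevalence was taken as approximately 14% of adult prevalence.

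Section 11.2.1 sets the trial at 175 children per arm, 350 in all.

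**The concern.** If every clinic has the same sampling fraction, clinic sizes must rise and fall with expected counts. In Table 5.1 they do not: the clinic with the most expected positives is given fewer numbers than a clinic with about 60% as many (479/790 = 0.61). A fraction of 0.175 also cannot be read off any row, nor off the totals.

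This matters because section 5.3.1 gives the clinic sizes a working role: they set how many pre-randomised study numbers each clinic receives. If the printed column were used to prepare the lists, some clinics would hold lists much shorter than the rule intends and others much longer, and recruitment would not be proportional to size as stated.

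**Working it through.** **Inputs.** Population, prevalence, expected count and final size by clinic are from Table 5.1. The target of 350 is 2 × 175, from section 11.2.1.

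**Step 1: are the other columns aligned?** Population × prevalence on the same row gives 374.6, 647.0, 495.3, 789.8, 478.7, 436.4 and 318.8. The printed expected counts are 375, 648, 494, 790, 479, 436 and 318. All agree to within about 1.3 children, so these columns are in the right rows.

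**Step 2: the plan's own figure.** Final size = 0.175 × expected count.
- Sum of expected counts: 375 + 648 + 494 + 790 + 479 + 436 + 318 = 3,540.
- 0.175 × 3,540 = 619.5. For PHC1 to PHC6 only, 0.175 × 3,222 = 563.9.
- Sum of printed sizes: 32 + 37 + 64 + 49 + 78 + 47 + 43 = 350.

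The printed sizes are not reproduced with seven clinics or with six. The fraction that gives 350 from seven clinics is 350/3,540 = 0.0989.

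**Step 3: proportional sizes on each clinic's own row.** Size = 350 × expected/3,540.

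| Clinic | Expected | 0.175 × expected | Proportional size | Printed | Printed/expected | Printed/expected of row above |
|---|---|---|---|---|---|---|
| PHC1 | 375 | 65.6 | 37.1 | 32 | 0.085 | 0.101 (PHC7) |
| PHC2 | 648 | 113.4 | 64.1 | 37 | 0.057 | 0.099 |
| PHC3 | 494 | 86.5 | 48.8 | 64 | 0.130 | 0.099 |
| PHC4 | 790 | 138.3 | 78.1 | 49 | 0.062 | 0.099 |
| PHC5 | 479 | 83.8 | 47.4 | 78 | 0.163 | 0.099 |
| PHC6 | 436 | 76.3 | 43.1 | 47 | 0.108 | 0.098 |
| PHC7 | 318 | 55.7 | 31.4 | 43 | 0.135 | 0.099 |

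On the same row the implied fractions run from 0.057 to 0.163, and none is 0.175. Against the row above they are all between 0.098 and 0.101.

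**Step 4: is the shift the only explanation that fits?** The correlation of printed size with expected count is 0.05 on the same row and 0.9999 against the row above. After the one-row shift the largest deviation is 0.56 of a child, at the 32 (31.4 rounded up so that the column sums to 350). The unshifted column and each of the other five cyclic shifts have a largest deviation above 30 children.

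**Step 5: size of the error.** Printed size minus own-row size, with PHC7 taken as 32: PHC1 −5, PHC2 −27, PHC3 +15, PHC4 −29, PHC5 +31, PHC6 +4, PHC7 +11 (sum 0).

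**Step 6: how far the open inputs move the answer.**
- *PHC7 prevalence.* 0.14 × 16.59 = 2.32, whereas the table uses 1.66 (1.66/16.59 = 10%). Suburbs 1 to 6 follow the 14% rule. With 2.3226%, PHC7 would expect 19,203 × 0.023226 = 446, the total would be 3,540 − 318 + 446 = 3,668, and the fraction 350/3,668 = 0.095. The sizes would be 35.8, 61.8, 47.1, 75.4, 45.7, 41.6 and 42.6.
- *Six clinics.* If these were PHC1 to PHC6, which is an assumption, the fraction would be 350/3,222 = 0.109 and the sizes 40.7, 70.4, 53.7, 85.8, 52.0 and 47.4.

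Neither variant reproduces the printed column or the 0.175.

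**The case against.** The arithmetic is hard to contest; the fair objections concern consequence and remedy.

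- **The comparison of arms is untouched.** Randomisation is 1:1 within each clinic, the total is still 350, and the power statements in section 11.2.1 use no clinic sizes. This stands in full.
- **The table may not be the source of the live lists.** It is headed as an expected sample size, and the protocol does not show the lists themselves. This also stands: a reader might infer that numbers were in fact sent to the wrong clinics, but the document shows only that the printed table breaks its own rule.
- **Lost or unfilled places are not shown.** A reader might infer that children at PHC2 and PHC4 would be turned away when their lists ran out, and that PHC3 and PHC5 could not fill theirs. No section says that a clinic closes at its quota or that a list cannot be extended. The longer lists need only 64/494 = 13% and 78/479 = 16% of expected positives.
- **The PHC7 figure is not settled.** A reader might take 2.32% as the right value. Section 4.2 says approximately 14% and gives a range whose lower end, 1.6%, fits 1.66%. The school survey value for that suburb, 1.79%, is also nearer to 1.66%. What is shown is an inconsistency.
- **The clinic count is a conflict across the document.** Six appears in sections 3.3, 4.1, 5.2 and 5.3.1; seven in sections 1.3, 5.1 and 7.1 and in Table 5.1. PHC1 to PHC6 populations sum to exactly 120,182, the total quoted in section 4.2, so PHC7 may have been added later; that is inference.
- **0.175 may be left over from a larger target.** Section 11.2.1 does mention a lower sample size, but the protocol does not confirm the link, and the figure would still be wrong for this table.

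**Conclusion.** The error is confirmed. Under section 5.3.1's own rule both the stated fraction and the per-clinic sizes in Table 5.1 are wrong: 0.175 should be about 0.099 for 350 children from 3,540 expected, and the final-size column is one row too low, with PHC7's figure in the PHC1 row. The largest discrepancies are −29 (PHC4), −27 (PHC2), +31 (PHC5) and +15 (PHC3).

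These sizes assume seven clinics and the expected counts as printed; Step 6 shows that the open inputs change the exact numbers but do not rescue the table. The practical consequence is conditional: study-number allotments per clinic are wrong if the table is used as printed. The documents do not support a claim of bias, of lost power, or of children actually excluded from the trial.

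**What to change.** 1. Settle the number of clinics and make sections 1.3, 3.3, 4.1, 5.1, 5.2, 5.3.1 and 7.1, Figure 1.1, and Tables 4.1 and 5.1 agree.
2. Reconcile PHC7's 1.66% with the 14% rule in section 4.2, which gives 2.32%: either apply the rule or state why this suburb departs from it.
3. Recompute the final column of Table 5.1 on each clinic's own row and state the fraction that results. With seven clinics and the present inputs the column is 37, 64, 49, 78, 47, 43, 32 (sum 350) and the fraction about 0.099.
4. Check the randomisation lists already issued against the corrected table, record which column they were built from, and extend any that are short.

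The first three steps are edits to text and tables. The fourth is a check of existing lists, with extra numbers generated only where a list is short; if enrolment is under way this needs care so that numbers already assigned stay unchanged. No additional participants are needed.
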